### Study procedures

#### Preparation

A pre-test was carried out in two primary healthcare clinics that were not in the study sample to confirm the strengths and weaknesses of the developed questionnaires. Patients of differing ages, genders, education levels and languages were interviewed and comments on the interview and questionnaire were recorded. Similar steps were applied to the provider questionnaire. Following that, all necessary changes and improvements to the questionnaire were made. Also, the study team did a trial run of the processes for data collection such as tracing patient medical records and interviewing patients and providers. The duration taken for each of these processes was also recorded. This allowed for further refinement of the data collection process and estimation of missing medical records, which can be accounted for in the sample size calculation.

This study recruits fieldworkers who are either medical or pharmacy graduates as data collection requires fieldworkers to be familiar with extracting data from medical records. Fieldworker training included the conduct of quantitative data collection such as manual data extraction from paper-based records, patient recruitment procedures and interview techniques.

#### Data collection period

The availability of documents and number of fieldworkers were taken into consideration when planning the data collection processes. Data for RCR will be collected for 31 time points (i.e. in months): (i) from November 2016 to June 2017 (pre-intervention) and (ii) from August 2017 to June 2019 (post-intervention). To keep the workload manageable and prevent exhaustion among the study team members, data collection for the 31 time points was divided into four phases, one pre-intervention phase and three post-intervention phases. Data collection phases were also decided based on the feasibility of recruiting for patient interviews during the fasting month. The data collection period for each phase is indicated in Figure 3. Each team is led by one team leader and four fieldworkers.

**Figure 3. f3:**
[figure not shown]
Study timeline and data collection period for EnPHC-EVA: Facility.

#### Quality control

Validation rules were embedded within the mobile applications to limit data entry error. The information captured will be uploaded to a central database with continuous monitoring by a data management team that performs quality checks and addresses discrepancies. The final captured data will undergo a systematic data cleaning process preceding data analysis. There is a full audit trail for data management which covers data entry and any amendments to the data. This measure will ensure that all the changes are monitored and there will be no accidental deletion.

### Target sample size and sampling

#### Retrospective chart review

Data analysis for RCR will use two methods – DiD analysis and interrupted time series (ITS) analysis. For DiD analysis, the sample size was calculated using *clustersampsi* in STATA version 14.2 (StataCorp, 2015).

First for T2DM, 1800 patient visits (900 in each arm) were needed to have 80% power to detect a relative change of 28% in the proportion of the patients receiving an annual HbA1c test from the baseline proportion of 52.5% (Mastura *et al*., 2011). This sample size was calculated while taking into account the estimated cluster effect [intracluster correlation (ICC) = 0.091] (Singh *et al*., 2015; Solorio *et al*., 2015). The minimum sample size was rounded up to 2000 or a cluster size of 50 patient visits per clinic. Therefore, the final target sample size for T2DM was 84 patient visits per clinic, after adjusting for an estimated 40% untraceable records.

Second, for hypertension, 1760 patient visits (880 in each arm) were needed to have 80% power to detect a 28% relative change in the proportion of hypertension patients with at least one lipid profile from the baseline proportion of 46% (Wong *et al*., 2015). This calculation took into account the estimated clustering of this outcome at the clinic level (ICC = 0.076) (Singh *et al*., 2015). After adjusting for 40% potentially untraceable records, the sample size required for hypertension patient visits was also 84 patient visits per clinic.

For ITS analysis, a minimum of 100 patient visits per arm at each time point is needed (Wagner *et al*., 2002). A minimum of eight time points was needed for both before and after intervention. In this study, eight time points pre-intervention and nine time points post 15-month intervention were chosen to evaluate the trend and level change over time. For each clinic, the estimated sample size required is ten patient visits for each disease. The final sample size after accounting for 40% untraceable records was 17 patient visits per clinic for each disease.

Systematic random sampling is used to sample the medical records by creating a sampling frame from the patients’ register either in a paper or in an electronic format. In facilities where neither of these is available, the lists are created from patient appointment books.

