### Data analysis

The data will be analysed using STATA version 14 and R version 3.3.2 (StataCorp, 2015; RStudio Team, 2016; R Core Team, 2017). Descriptive data will be expressed as means or proportions with their corresponding 95% confidence intervals or medians with interquartile ranges. Statistical significance will be determined with a 2-sided *P*-value with *P* < 0.05. A complete case analysis will be used.

An interim analysis will be conducted at the end of Phase 2. A research management team is tasked to monitor the study at the end of Phase 2 and Phase 3b. The research management team will review and comment on the interim and final analysis.

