#### Difference-in-differences

DiD analysis will be used to analyse all outcome measures. DiD analysis measures the average effect of the interventions, taking into account two differences: first is the difference between the intervention and control arm and second is the difference between pre- and post-intervention (Gertler *et al*., 2011; Dimick *et al*., 2014). As this is a large-scale field experiment, the difference at baseline is often not negligible and must be accounted for when measuring the intervention effect.

A multivariable model that controls for patient- and clinic-level covariates will be used. Details on the key covariates for each objective can be found in Appendix F. For RCR, patient visits from November 2016 to June 2017 will be grouped to estimate outcome levels in the pre-intervention phase and those from October 2018 until June 2019 will be grouped to estimate outcomes after 15 months of intervention.

Generalised estimating equations will be used to estimate the parameters for both linear and non-linear outcomes while adjusting for clustering at the clinic level. Thus, cluster robust standard errors will be reported. In addition, the key assumptions for DiD analysis which are ‘common shocks’ and ‘parallel trends’ will be checked where trend data are available.

The ‘geeglm’ function from the ‘geepack’ package in *R* will be used to perform the analysis (Yan, 2002; Yan and Fine, 2004; Højsgaard *et al*., 2005). For RCR outcome measures that will be reported as proportions, the DiD estimates will be reported as odds ratios with 95% confidence intervals. For provider survey and patient exit survey outcome measures, the DiD estimates will be reported as changes in means with 95% confidence intervals.

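### The 80% power stated for the difference-in-differences analysis comes, for T2DM, from a single-period two-arm calculation, and the hypertension size does not follow from its own inputs

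*Protocol article*

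**What the plan says.** Under Target sample size and sampling, Retrospective chart review, the protocol article begins "For DiD analysis, the sample size was calculated using" a named Stata command. For T2DM it then states "1800 patient visits (900 in each arm) were needed to have 80% power to detect a relative change of 28" per cent, "from the baseline proportion of 52.5" per cent, with "intracluster correlation (ICC) = 0.091". For hypertension it states "1760 patient visits (880 in each arm) were needed to have 80% power to detect a 28% relative change", "from the baseline proportion of 46" per cent, with an ICC of 0.076. The T2DM minimum is rounded up to 50 visits per clinic, and an allowance for 40% untraceable records gives 84 visits per clinic for each disease. The section gives no correlation between periods and does not say whether 84 is per period or in total.

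Under Difference-in-differences, "DiD analysis will be used to analyse all outcome measures". For the chart review, visits from November 2016 to June 2017 form the pre-intervention group and visits from October 2018 to June 2019 form the post-intervention group, in both arms. The model is a GEE clustered on clinic with patient- and clinic-level covariates.

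**The concern.** A DiD estimate subtracts a sampled baseline difference from a sampled follow-up difference. The baseline adds sampling noise, while the correlation of each clinic with itself over time removes some between-clinic variance. A calculation built from one baseline proportion, one target proportion and one ICC contains neither effect, so its power belongs to a different contrast.

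This is the only power statement for the processes of care and intermediate clinical outcomes, which are the primary objective. If the 80% does not describe the planned contrast, a reader cannot judge from it whether the study was sized for the effect it names. The error could run in either direction.

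**Working it through.** **Inputs from the article.** Two-sided test at 0.05 (Data analysis: "Statistical significance will be determined with a 2-sided" P-value below 0.05); 20 clinics per arm (Study design and study sites). T2DM: p1 = 0.525, p2 = 0.525 × 1.28 = 0.672, ICC = 0.091. Hypertension: p1 = 0.46, p2 = 0.46 × 1.28 = 0.5888, ICC = 0.076. Traced visits per clinic after rounding: 50.

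**Assumed, because not given.** The correlation r between a clinic's true pre and post effects, and the split of visits between periods.

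**Step 1: reproduce the T2DM size.** For a single-period comparison with k = 20 clinics per arm and t on 38 df:

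n = (t.975 + t.80)² × [p1(1−p1) + p2(1−p2)] / (p2−p1)², and m = n(1−ICC) / (k − n × ICC).

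- (2.0244 + 0.8512)² = 8.269
- n = 8.269 × (0.2494 + 0.2204) / 0.147² = 179.8
- m = 179.8 × 0.909 / (20 − 179.8 × 0.091) = 163.4 / 3.641 = 44.9, so 45 per clinic
- 45 × 40 = 1800, the stated figure

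No second period enters.

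**Step 2: the same formula for hypertension.**

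- n = 8.269 × (0.2484 + 0.2421) / 0.1288² = 244.5
- m = 244.5 × 0.924 / (20 − 244.5 × 0.076) = 225.9 / 1.418 = 159.3 per clinic, or 160 × 40 = 6400 visits against the stated 1760

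The denominator is close to zero, so m is very sensitive to the inputs. Power shows the gap on a steadier scale. At the stated 44 per clinic (1760 / 40), SE = √{0.4905 × [0.076 + 0.924/44] / 20} = 0.0488, the ratio is 0.1288 / 0.0488 = 2.64, and power is 73% (75% with a normal reference). At the rounded 50 per clinic it is 74%. A target of 60%, an ICC of about 0.060, or an undocumented baseline correlation of about 0.40 would each give 44 per clinic. The article does not show which, if any, was used.

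**Step 3: power of the planned DiD contrast.** On clinic means, each clinic-period cell has variance p(1−p)[ICC + (1−ICC)/m]. The covariance between a clinic's two periods is r × ICC × √[p(1−p) × p′(1−p′)]. The DiD variance sums each arm's two cell variances, less twice the covariance, and divides by 20.

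T2DM at 50 visits in each period:

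- Cell factor: 0.091 + 0.909/50 = 0.1092
- r = 0: V = (3 × 0.2494 + 0.2204) × 0.1092 / 20 = 0.00529; SE 0.0727; ratio 0.147 / 0.0727 = 2.02; power 50%
- r = 0.6: the covariance terms total 2 × 0.6 × 0.091 × (0.2494 + 0.2344) = 0.0528; V = (0.1057 − 0.0528) / 20 = 0.00265; SE 0.0514; ratio 2.86; power about 80%

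Results with t on 38 df, risk-difference scale:

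| Visits per clinic (pre, post) | Disease | r = 0 | 0.5 | 0.6 | 0.8 | r for 80% |
|---|---|---|---|---|---|---|
| 50, 50 | T2DM | 50% | 73% | 80% | 93% | 0.61 |
| 50, 50 | Hypertension | 45% | 66% | 72% | 87% | 0.71 |
| 80, 90 | T2DM | 53% | 78% | 85% | 97% | 0.53 |
| 80, 90 | Hypertension | 48% | 72% | 79% | 94% | 0.61 |
| 25, 25 | T2DM | 44% | 62% | 67% | 80% | 0.81 |
| 25, 25 | Hypertension | 38% | 54% | 58% | 69% | 0.95 |

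The 80 and 90 come from reading the time-series requirement of ten visits per clinic as monthly: 8 × 10 pre and 9 × 10 post. The 25 and 25 apply if 50 visits cover both periods. The log-odds scale, closer to the planned odds ratios, agrees within about 2 points.

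**The case against.** The strongest reply is that the calculation may do no harm. The same 40 clinics are observed twice, each pooled over eight or nine months, so r = 0 is an extreme bound. At 50 visits per period, break-even corresponds to a correlation of observed clinic means of only about 0.51 (0.61 × 0.091 / 0.1092) for T2DM and 0.57 (0.71 × 0.076 / 0.0945) for hypertension. Pair matching and covariate adjustment could add precision that the table does not credit. The planned confidence intervals will show the precision achieved, and an article may leave an autocorrelation value to the full protocol.

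Much of this stands. A reader might infer that the DiD analysis is underpowered, or that it reaches 80% only with strong correlation between periods. The article does not support either: if the visits are per period the condition is moderate, and above it power exceeds 80%. A strong correlation is needed only if the 50 visits are split across both periods. A reader might also infer that both sizes are post-period calculations. That is shown for T2DM only; the origin of 1760 is unknown.

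What does not stand is the appeal to condensation. The article itself states the inputs, the power and the analysis they serve, and for T2DM those inputs give the stated size without any DiD term.

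**Conclusion.** The point holds in limited form. The T2DM 80% belongs to a single-period two-arm comparison and is labelled as power for DiD. Power for the planned contrast is not fixed by anything in the article: with 50 visits per clinic in each period it runs from about 50% to 93% for T2DM and from 45% to 87% for hypertension as r goes from 0 to 0.8. The direction of the error is unknown. These figures rest on an assumed r, an assumed split of visits between periods, and an unadjusted, unmatched model.

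The hypertension discrepancy is separate and does not depend on r: 1760 visits give about 73%, not 80%, even in the single-period comparison that reproduces T2DM.

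**What to change.** In Target sample size and sampling, Retrospective chart review:

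1. Describe 1800 as the result of a single-period, two-arm comparison.
2. State the visits per clinic in each period, and whether 84 is per period or in total.
3. Give DiD power for both diseases at the visits actually sampled, over a stated range of r. The eight baseline months can inform r, but they do not identify it across the 15 months of intervention between the two periods and may overstate it, so a range is needed.
4. Reconcile the hypertension baseline, relative change and ICC with 1760, or correct the size or the power.

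The cost is one recalculation and a few sentences. No extra visits and no change to the analysis are needed. The only downside is that the restated power may be less favourable than 80%.

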## Methods

### Study design and study sites

The EnPHC-EVA: Facility study is a quasi-experimental controlled study which involves 20 intervention and 20 control clinics. We drew on a methodology developed by Imai, King and Nall (Imai *et al*., 2009). After considering regional representativeness, budget and capacity to implement EnPHC interventions, 20 matched pairs from two states (Johor and Selangor) were selected to be the study sites. The clinics were matched based on the criteria listed in Table 2 (Family Health Development Division, 2018). In addition, ArcGIS software (ESRI, 2011) was used to ensure that the matched pairs were in different districts to minimise patients’ overlap. The matched pairs were then randomly allocated to the ‘intervention’ or ‘control’ arm of the study by ‘flipping a coin’.

**Table 2. tbl2:** Clinic inclusion and matching criteria

Clinic inclusion criteria	Clinic matching criteria
Has at least two medical officers Clinics with attendances between 300 and 800 patients per day	Number of medical officers Number of Family Medicine Specialist Location: Rural/Urban Availability of Tele-Primary Care system Annual patient attendance

There are nine and 11 matched pairs, in Selangor and Johor states, respectively. Figure 2 shows the matching pairs in both Johor and Selangor states, where intervention clinics were identified with crosses.

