### Outcome measures

Outcome measures used in this study are captured using different data collection tools and are summarised in Table 4. It is anticipated that improvements of blood pressure, lipid levels and glycaemic control will be observable after at least one year as changes have been detected after 12.5 months of implementation in similar evaluation studies (Norris *et al*., 2001). Hence, for post-intervention, information on processes of care (investigations, counselling and prescribing patterns) will be gathered via RCRs 15 months after implementation.

**Table 4. tbl4:** Outcome measures of the EnPHC-EVA: facility study

Outcomes	Indicators		Data Source
	T2DM	Hypertension	
Process of care	Proportion of Patients whose BP and glucose were measured at every visit Patients with HbA1c tests done at least once over the past three months Patients with weight and BMI assessed at least once over the past six months Patients with the following examinations done at least once a year: lipid profile tests, serum creatinine, blood urea nitrogen and urine albumin tests, eye examination (visual acuity and fundus), foot examination and liver function test Patients with cardiovascular risk assessment done within the past one year Patients who received counselling: exercise, dietary Patients who received pharmacotherapy: lipid lowering drugs, insulin and antihypertensives	Proportion of Patients with BP measured at every visit Patients with fasting blood glucose, serum creatinine, urine albumin and lipid profile measured at least once a year Patients with electrocardiogram and cardiovascular risk assessment done within the past one year Patients who received counselling: exercise, dietary Patients who received pharmacotherapy: antihypertensives	RCR
Intermediate clinical outcomes	Proportion of Patients with HbA1c ≤ 7% Patients with BP ≤ 135/75 mmHg Patients with LDL-C ≤ 2.6 mmol/L Patients with HDL-C > 1.0 mmol/L (male) or HDL-C > 1.2 mmol/L (female)	Proportion of Patients with BP < 140/90 mmHg Patients with LDL-C ≤ 2.6 mmol/L Patients with HDL-C > 1.0 mmol/L (male) or HDL-C > 1.2 mmol/L (female)	RCR
Patient disease awareness	Proportion of patients who know their diagnosis		Patient exit survey

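### The 80% power for T2DM refers to annual HbA1c testing, which Table 4 does not list; power for the listed three-month indicator is not stated

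*Protocol article*

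**What the plan says.** Under Target sample size and sampling, Retrospective chart review, the protocol article states that 1800 T2DM visits (900 per arm) are "needed to have 80% power to detect a relative change of 28" per cent in the "proportion of the patients receiving an annual HbA1c test from the baseline proportion of 52.5" per cent, allowing for "intracluster correlation (ICC) = 0.091". The figure is rounded up to 2000 visits, or 50 per clinic, and raised to 84 per clinic for 40% untraceable records. No other power statement for T2DM is given.

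Under Outcome measures, Table 4 defines HbA1c testing for T2DM as "Patients with HbA1c tests done at least once over the past three months". A separate T2DM line covers yearly checks: "Patients with the following examinations done at least once a year: lipid profile tests, serum creatinine, blood urea nitrogen and urine albumin tests, eye examination" and so on, ending with foot examination and liver function. HbA1c is not on that line. The only other HbA1c entry is a control measure, "Patients with HbA1c ≤ 7" per cent, which is not about testing.

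**The concern.** The two sections fix different definitions of the same process measure. Table 4 distinguishes yearly from three-month windows and puts HbA1c testing in the three-month group, while the sample size uses a yearly window. The hypertension calculation does not have this problem: it is sized on lipid profile testing, which Table 4 lists.

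A colleague reading the article would take 80% as the power for the HbA1c testing indicator in Table 4. A null result on that indicator could then be read as stronger evidence of no effect than the design supports. Two windows in the text also leave the choice between them open, and an interim analysis at the end of Phase 2 is planned before the final analysis.

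**Working it through.** **Inputs from the protocol article**
- Baseline 0.525, relative change 28%, ICC 0.091, 900 visits per arm (Retrospective chart review)
- 20 clinics per arm (Study design and study sites), so m = 900/20 = 45 visits per clinic
- Two-sided 5% significance level (Data analysis)

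**Step 1: reproduce the plan's figure.**
- Target proportion: 0.525 × 1.28 = 0.672, a difference of 0.147 (14.7 points).
- Design effect: 1 + (m − 1) × ICC = 1 + 44 × 0.091 = 5.004.
- Effective size per arm: 900/5.004 = 179.9.
- Standard error: √[(0.525 × 0.475 + 0.672 × 0.328)/179.9] = √(0.4698/179.9) = 0.0511.
- Noncentrality: 0.147/0.0511 = 2.876. Noncentral t with 38 degrees of freedom and critical value 2.024 gives power of 80.0%.
- At m = 44 the power is 79.9%, so 45 is the smallest cluster size that reaches 80%. The stated 900 per arm is reproduced exactly. At the rounded 50 per clinic, power is 80.7%.

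**Step 2: what carries over to the three-month indicator.** Anyone tested in the past three months was also tested in the past year. In the same patients at the same date, the three-month proportion therefore cannot exceed the annual one. The document gives neither a baseline nor an ICC for three-month testing, so the baselines below are assumptions and the ICC is held at 0.091.

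**Step 3: power at 45 visits per clinic (t-based, same formula).**

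| Assumed three-month baseline | 28% relative change to | Power | 14.7-point change to | Power |
|---|---|---|---|---|
| 45% | 57.6% | 65% | 59.7% | 79% |
| 40% | 51.2% | 55% | 54.7% | 79% |
| 30% | 38.4% | 38% | 44.7% | 81% |
| 25% | 32.0% | 30% | 39.7% | 84% |

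Worked row, 40% with relative change: the difference is 0.112; the standard error is √[(0.40 × 0.60 + 0.512 × 0.488)/179.9] = 0.0522; the noncentrality is 2.146; power is 55%.

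**Step 4: would more visits help?** The time-series requirement of ten visits per clinic per month, pooled over the eight pre-intervention and nine post-intervention months used for the difference-in-differences analysis, gives about 80 and 90 visits per clinic. At 90 per clinic with the relative change, power is 59% at a 40% baseline and 41% at 30%. As m grows without limit, the effective size per arm tends to 20/0.091 = 219.8, and power at a 45% baseline tends to 74%. Under the relative target, no cluster size reaches 80% at a baseline of 45% or below.

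**The case against.** The strongest reply is that a loss of power has not been shown. The 28% was set for the annual measure. If the intended effect is the same number of percentage points, power stays close to or above 80%, as the last column of the table shows. This stands: the article says relative, but nothing commits the sponsor to that figure for a different indicator.

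A reader might go further and infer that power for the listed indicator is as low as 20%. That comes from spreading a 52.5% annual rate evenly over the year: 1 − (1 − 0.525)^(1/4) = 17%, and a 28% relative change from there has about 20% power. The document does not support that anchor. Charts are sampled from visit registers and appointment books, so every sampled patient is attending the clinic, and testing that clusters around visits would put the three-month figure above 17%.

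A reader might also infer that the headline T2DM outcome is underpowered, that the annual measure will never be reported, or that the whole T2DM sample is undermined. The article ranks no process indicator above the others. That the annual measure will go unreported is only an inference from its absence in Table 4. Several other T2DM indicators keep a yearly window. Nor does the mismatch bias any estimate, and confidence intervals are planned.

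None of this reconciles the two sections. Condensing a fuller protocol can explain an omission, but not two different explicit definitions.

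**Conclusion.** The point holds as an inconsistent outcome definition, not as an arithmetic error. The calculation is right for annual HbA1c testing; Table 4 does not list that measure, and power for the measure it does list is unstated.

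How far that power falls short of 80%, if at all, cannot be settled from the document. It depends on the three-month baseline, on that indicator's ICC (taken here as 0.091) and on whether the target is relative or absolute. Over assumed baselines of 45% down to 25%, power runs from about 65% to 30% on the relative target and from 79% to 84% on the absolute one. The bound that three-month testing cannot exceed annual testing applies within the same patients. The 52.5% comes from a cited source, so the study clinics may start elsewhere.

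This should be fixed. It does not call the sampling, the number of clinics or the analysis model into question.

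**What to change.** Reconcile the sample-size section with Table 4 in one of two ways:

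- **Preferred:** add to Table 4, as a T2DM process indicator, the proportion with an HbA1c test in the past year. State that the 80% power refers to it, use the same look-back before and after the intervention, and keep the three-month indicator as a further outcome.
- **Otherwise:** restate the power for the three-month indicator from its observed pre-intervention proportion and ICC, and say whether the target change is relative or absolute.

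The cost is a table and wording change, plus one more indicator derived from test dates in the same records. The chart review already covers other yearly tests, so no new data source is needed.

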Improve information systems for providers	A single electronic information system that integrates existing systems, provides options for manual and digital entry and supports the health system as it moves towards its long-term Tele-Primary Care (TPC) transformation.	Paper-based clinical records, legacy TPC systems and TPC-OHCIS	Paper-based clinical records, legacy TPC, TPC-OHCIS v 1.1, mobile patient and provider apps

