**(vi) Improved organisational practices**			
Primary Health Team (PHT) and FHTs	Two or more FHTs are formed within a single PHT for each clinic. Each FHT will function as a multidisciplinary unit that provides services for all patients within a zone in a catchment area. At a minimum, each FHT core team will include a family medicine specialist (FMS), a MO, an AMO/nurse and a care coordinator (CC). FMSs and CCs will work on multiple FHTs within a clinic, ensuring that care across FHTs is uniform. FHT will not just assess, diagnose and manage its patients but will be responsible for educating, coordinating referral and maintaining good record keeping of each assigned zone.	Physician-centred care with limited roll out of family doctor concept (FDC)	FHTs
Primary triage and standardising signage at clinics	A primary triage and improved standardised signages are introduced to decongest the registration counter and ensure smooth navigation for patients as they go through the check points for a visit within the clinic.	Limited availability	Available
CC	CCs are essential for creating and maintaining a strong link between patients and their FHT providers. CCs will work closely with community workers, providers at screening centres and secondary and tertiary care centres to keep FHTs informed about the status of patients and any population changes in catchment areas. They are also responsible for connecting patients with support services and managing referrals and counter-referrals. CC will need a qualification of paramedic (either AMO or nurse) who has been working with the Ministry of Health and received certified training in primary healthcare or NCD management or senior paramedics with five days training in NCD management, ICP, communication and management.	Not available	Available

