There are several limitations in this study. First, it is not possible to distinguish the effects from each activity of the intervention as it is a complex intervention. Next, the findings of this study will only be generalisable to clinics with similar characteristics. Long-term outcomes such as micro- and macrovascular complications and behavioural changes could not be measured as the study duration is not sufficient to observe these changes. Missing data arising from untraceable records and incomplete documentation in medical records may introduce bias to the findings. This could be improved by integrated electronic information systems in the long run.

In summary, this study will provide evidence on the effectiveness of a complex intervention designed to reduce the number of undiagnosed T2DM and hypertension patients as well as improve the overall quality of care in this group of patients to delay overall disease progression.

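### Untraceable records are handled only by a larger sample and complete cases, although the package alters record keeping in intervention clinics, so tracing may change differently by arm and period

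*Protocol article*

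**What the plan says.** Under Target sample size and sampling (Retrospective chart review), the T2DM sample for the DiD analysis is first rounded: "The minimum sample size was rounded up to 2000 or a cluster size of 50 patient visits per clinic". It is then inflated: "the final target sample size for T2DM was 84 patient visits per clinic, after adjusting for an estimated 40% untraceable records". Hypertension gets the same allowance: "After adjusting for 40% potentially untraceable records, the sample size required for hypertension patient visits was also 84 patient visits per clinic". The monthly samples for the interrupted time series go from 10 to 17 visits per clinic and disease on the same basis.

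Under Data analysis the rule for missing data is one sentence: "A complete case analysis will be used". The Discussion lists a limitation: "Missing data arising from untraceable records and incomplete documentation in medical records may introduce bias to the findings". It adds that integrated electronic systems could improve this in the long run.

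The Data extraction form section says that chart data come from the clinics' own paper or electronic records. Table 1 describes changes to those records as part of the package. Component (iv) includes "A single electronic information system that integrates existing systems" and a visit checklist that builds a database of services. Component (vi) gives family health teams a duty of "maintaining good record keeping of each assigned zone" and replaces unstandardised disease books with a common NCD care form.

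**The concern.** The 40% allowance is used only to restore the number of analysable visits. It says nothing about whether the visits that are found represent those that were sampled. The issue here is whole records never located, not missing results inside a located record.

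DiD removes selection that stays constant over time within an arm. It does not remove a change in selection that occurs in one arm after the start, because that change has the same arm-by-period form as the treatment effect. The planned checks of parallel trends (DiD) and of equivalent baseline trends (interrupted time series) rest on pre-intervention data, so they cannot show it. Matching on Tele-Primary Care availability balances systems at baseline only.

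The package acts on the forms and record practices from which outcomes are read, so such a change is plausible. The article does not link the two or describe any comparison of tracing by arm and period. At stake is whether a reader can tell a change in care from a change in which charts were found. That matters for a project meant to inform national expansion.

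**Working it through.** **1. The plan's own figures.** Inputs are 50 and 10 analysable visits per clinic and 40% untraceable.
- DiD: 50 / (1 − 0.40) = 83.3, rounded up to 84.
- Time series: 10 / (1 − 0.40) = 16.7, rounded up to 17.

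Both reproduce. The underlying 900 T2DM visits per arm also reproduces. With 20 clinics of 45 visits and ICC 0.091, the design effect is 1 + 44 × 0.091 = 5.004. Power for 52.5% against 67.2% is then 80.0% (unpooled variance, t on 38 degrees of freedom). There is no arithmetic error here.

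**2. Scale of the allowance.** For one sample of 84 per clinic, 84 × 40 = 3,360 visits per disease. At 40%, 0.40 × 3,360 = 1,344 would not be found.

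**3. Planned effect.** The design aims to "detect a relative change of 28% in the proportion of the patients receiving an annual HbA1c test from the baseline proportion of 52.5" per cent. That is 0.28 × 52.5 = 14.7 points, to 67.2%, an odds ratio of (0.672/0.328) / (0.525/0.475) = 1.85.

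**4. Illustration of the mechanism.** The documents give neither the outcome gap nor any change in tracing, so both are assumed. Let p be the outcome proportion among traced visits, g the traced-minus-untraced gap, and c0 and c1 the traced shares before and after in the intervention arm. Control tracing stays at c0, there is no true effect, and newly traced visits come from the previously untraced pool. Then

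observed post proportion = [c0·p + (c1 − c0)(p − g)] / c1, so the spurious DiD = −g (c1 − c0) / c1.

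With c0 = 0.60, the size of the shift in points is:

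| Gap g | c1 = 0.70 | c1 = 0.80 | c1 = 0.90 |
|---|---|---|---|
| 10 points | 1.4 | 2.5 | 3.3 |
| 20 points | 2.9 | 5.0 | 6.7 |
| 30 points | 4.3 | 7.5 | 10.0 |

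The shift is negative if untraced visits have the lower rate and positive if they have the higher rate. For g = 20 points and c1 = 0.80: 0.20 × 0.20 / 0.80 = 0.05. Starting from p = 52.5%, the post proportion is 47.5% (odds ratio 0.82) or, with the gap reversed, 57.5% (odds ratio 1.22). Five points is 5.0 / 14.7 = 34% of the planned effect. The whole table spans 1.4 / 14.7 = 10% to 10.0 / 14.7 = 68%.

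**5. When it vanishes.** The shift is zero if g = 0 or c1 = c0. It also cancels if control tracing changes in the same way. If control tracing rose to 70% while intervention tracing rose to 80%, the 20-point case would shrink to 5.0 − 2.9 = 2.1 points.

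**The case against.** The strongest reply is that no passage says tracing changes during the study, let alone by arm. In the information-systems row of Table 1, the EnPHC column still lists paper records and the legacy system, and the Discussion puts the gain from integrated systems in the long run. A duty of good record keeping does not in itself make a sampled chart easier to find. This stands. A reader might infer that tracing is bound to rise in intervention clinics, but the documents support only that it may change.

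A reader might also infer that the bias would appear as a spurious harm. That does not follow, because the sign depends on an unknown gap.

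Nor is the comparison unadjusted. The DiD model has patient- and clinic-level covariates, and the implementation checklist score also enters as a covariate. These can absorb measured differences in patient mix. They are not described as addressing tracing, and they cannot recover unmeasured differences in visits never found.

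Further, 40% is a planning allowance and not an observed loss. Contamination of control clinics is expected and would narrow any differential. The article already concedes bias from untraceable records in general terms, and details may sit in a fuller plan. All of this is fair. Yet complete-case analysis is a choice the article itself fixes, and its stated limitation does not reach the route through the intervention.

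**Conclusion.** The concern holds in conditional form. A large expected loss of records is met by sample inflation and complete cases, while the package alters record practices in intervention clinics by design. Tracing may therefore change differently by arm and period, and neither DiD nor the pre-trend checks would remove or reveal that.

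The documents fix neither the direction nor the size of any bias. The 5-point figure, in either direction against a planned 14.7, rests on three assumptions: a 20-point gap, a rise from 60% to 80% traced in the intervention arm, and no change in control. The documents do not show that bias will occur, and the sample-size arithmetic is sound. The point bears on what can be concluded from the chart-review outcomes and is cheap to settle with data.

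**What to change.** Keep one row for every sampled visit, traced or not, from the existing register or appointment-book frame: clinic, month, disease, traced yes/no, and record format where known. For periods already collected, any retained sampling lists could serve. Report traced proportions by arm and period, and analyse record tracing as an outcome in the same DiD model.

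If tracing differs by arm and period, add a two-sided sensitivity analysis, for example with untraced visits 10 to 30 points lower or higher than traced ones. Qualify any effect whose sign depends on that range. If the same gap d is assumed in all four arm-period cells, each cell mean is p − d + t·d, where t is the traced share. The full-sample DiD is then the traced-record DiD plus d times the DiD in the traced share. A 20-point differential in tracing would move it by 0.20 × 10 = 2 to 0.20 × 30 = 6 points either way.

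Use inverse-probability weighting only as a secondary analysis, where the register holds patient-level variables such as age and sex. Weighting by the traced proportion within clinic and month gives every traced visit in that cell the same weight. It leaves the cell mean unchanged and cannot correct selection inside the cell.

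The cost is a short log of untraced samples, a little extra analysis and possibly more cautious conclusions. If tracing proves stable, the main result is strengthened.
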